## Primary outcome

The intervention primarily aims at improving “self-care” as a multi-dimensional construct consisting of the five dimensions diet, exercise, self-monitoring of blood glucose (SMBG), foot care, and smoking behavior. This primary outcome is a patient reported outcome (PRO) and will be operationalized by the German version of the revised „Summary of diabetes self-care activities measure“ (10) (SDSCA). The English version of the revised SDSCA is a widely used, appropriate (24) valid and reliable tool with moderate test-retest-reliability (10) for capturing self-care behavior.

The German version (SDSCA-G) is based on a structured forward/backward translation of the original English instrument. The SDSCA-G will be deployed as part of paper-based questionnaire (see Appendix: Patientenfragebogen zur Erfassung der Selbstsorge) and consists of 11 items.

Scoring of items 1–10 (excluding smoking) uses days per week on a scale of 0–7 in which patients performed respective self-care tasks (24). For each group of items (e.g. diet) a mean number of days are calculated. The SDSCA scale is used as a continuous measure to determine if there are improvements compared to baseline at subsequent time points. As a result of strong ceiling effects, the ‘medication’ item is not included in the most recent recommended version [16].

No cut-off point has been determined to discriminate between adherence and non-adherence (24) and no minimal clinically relevant change in SDSCA ‘scores’ has yet been formulated (25). This means that, in order to determine a minimal clinically relevant change for this study, the research team needs to draw upon (i) published data on the degree of change in SDSCA values reported in interventions designed to improve self-management, and (ii) estimates about ‘realistic’ changes that the intervention can bring about.

The primary outcome used to assess the efficacy of the intervention is the difference in mean change in SDSCA-G ‘score’ of items 1-10 (excluding smoking) per patient compared to baseline (T0) after 9 months of intervention (T1) between both groups (PTC vs. TAU) determined on the basis of patients’ self-reports.

## Secondary outcomes

In light of the secondary objectives, the secondary outcomes of this study refer to:

1. The mean change in SDSCA-G 'score' of items 1-10 (excluding smoking) for each group (PTC vs. TAU) compared to baseline (To) after 18 months of intervention (T2), to assess sustainability of effects with reduced intensity of care management and enhanced by self-monitoring of blood-glucose
2. The mean change in each of the five dimension of self-care captured by the SDSCA-G instrument compared to baseline (To) for each group (PTC vs. TAU) at T1/T2 of intervention to assess the influence of the intervention on specific self-care behaviors
3. The mean change in physician-reported glycosylated hemoglobin A1c (HbA1c %) at T1/T2 compared to baseline among the subgroup of patients with a baseline value of HbA1c > 7.5 %. A 10 % improvement from the baseline value (25) after 9 months/18 months will be regarded as clinically relevant change.
4. The cumulative incidence of physician-reported (severe) symptomatic hypoglycemia at T1/T2 among those patients at risk of this event during the respective observation period. 'Symptomatic hypoglycemia' refers to hypoglycemia with blood glucose < 60 mg/dl, and 'severe symptomatic hypoglycemia' as those events of hypoglycemia, which necessitated external support. Patients are regarded 'at risk' of (severe) symptomatic hypoglycemia for the subsequent time period if they receive oral anti-diabetic medication and/or insulin therapy at To or T1.
5. The mean change in patient-reported HRQL, captured by the EuroQol instrument EQ-5D, at T1/T2 compared to baseline. EQ-5D is a 5-item, simple preference-based index measure which has frequently been applied in the measurement of HRQL in type 2 diabetes (including the United Kingdom Prospective Diabetes Study). The overall EQ-Index score (on a scale of 0 to 1) can be incorporated into Quality Adjusted Life-Years (QALY) for cost-utility analysis. A difference of 0.03 on overall EQ-Index score after 9 months/18 months will be considered to be clinically relevant (25).
6. The mean change in patient-reported self-efficacy, captured using the SES6-G instrument, a short and validated instrument with 6-items (26).
7. The equity-efficacy ratio calculated as the ratio between the change (compared to To at T1) in SDSCA-G 'score' of items 1-10 (excluding smoking), HbA1c% and EQ-Index among the lowest vs. highest socioeconomic group (including education, occupation, income and subjective social status) in both arms of the trial (PTC vs. TAU). This includes subgroup analyses for migrant populations.
8. Further secondary outcomes will be captured by the Client Socio-demographic and Service Receipt Inventory (CSSRI) (27, 28) and the financial family burden questionnaire. Both instruments have been adapted to the special needs of patients with type II diabetes and were

Dept. for General Practice and Health Services Research- University Hospital Heidelberg

„A multi-center, individual-level randomized, 18-month, parallel-group superiority trial to compare the efficacy of a complex primary care practice network-based care management intervention versus usual care in the improvement of self-care behavior among patients with type II diabetes and multiple comorbidities (GEDIMApplus)“

Version 1.0 – 29.10.2013

pretested before general application. CSSRI provides data on service utilization and refers to costs of health care provision and financial burden of informal care. Direct and indirect costs will be measured and analyzed from a societal perspective.

For an overview of all instruments used in this study to capture primary and secondary outcomes see Table 1. Physician reported secondary outcomes (HbA1c, events of hypoglycemia) are reported via a chart-review (for details see Chapter 10: Data collection).

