### 3. Methods

#### 3.1 General Aspects

The study is designed as a prospective, multicenter, two-armed, open-label, individual-level randomized controlled superiority trial (RCT). Since the main elements of the intervention are delivered by an NCM (for details see Chapter 8: Intervention/Study Implementation), it is feasible to have both intervention and control group based in each study center (i.e. in each PCP).

Eligible participants will be randomly selected from the overall patient population of 30 study centers (PCPs) and asked for their consent to take part in the study. Participating patients will be reported pseudonymized to the study central office (Dept. for General Practice and Health Services Research, AMV) and centrally randomized on an individual level by a clinical monitor, who acts as sole randomization authority. This person - not involved in care of the trial patients or analysis of data - will be responsible for allocation to control (treatment as usual, TAU) vs. intervention group (pathway to change, PTC) according to a pre-defined randomization schedule (for details see Chapter 7: Randomization). As illustrated in Figure 1, the intervention is additional to usual care. Blinding of either patients or practice teams is not possible due to the character of the intervention. The baseline (To) assessment of primary and secondary outcomes will be conducted prior to allocation of patients, and after allocation at 9 months (primary endpoint: T1), and 18 months (follow-up: T2) (Figure 1).

Both intervention and control group receive usual care. Usual care consists of diabetes care in the scope of the DMP Diabetes. Care for high-prevalence chronic comorbidities such as chronic obstructive lung disease (COLD), heart failure (HF) and coronary heart disease (CHD) are also organized in the scope of DMPs on a voluntary basis in the statutory health insurance system (16). Care for other diseases (chronic or acute) is managed by PCP physicians individually based on personal experience, guidelines and/or patients' preferences.

Patients allocated to the PTC-group will be subject to the 18-month care management intervention as add-on to usual care. This complex care management intervention consists of three main elements (Figure 1):

- (i) assessments by a net-case manager (NCM) including home visits,
- (ii) regular telephone-monitoring contacts and
- (iii) digital structured blood glucose monitoring (introduced after T1).

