## **Symptom and Needs Monitoring**

NCMs will deliver a regular telephone-monitoring using a structured monitoring list (see Appendix X). Content and frequency of the monitoring are fixed, but additional items may be determined by the PCP and the NCM. The NCM will deliver (at least) a total of 24 telephone-monitoring sessions according to a fixed schedule (2-weekly for a period of 6 months, monthly for the rest of the intervention period for patients in the PCT-group (Figure 1). Monitoring items contain new diagnoses, dyspnea, incidence/frequency/severity of hypoglycemia, blood pressure, weight, fatigue, medical/social problems and follow-ups on previously mentioned problems and hospitalizations since the last contact. The monitoring list (see Appendix: Studienhilfsmittel "Checkliste Telefonmonitoring") has been developed based on experiences of GGM in prior studies (GEDIMA). Item responses include 'red flags' according to the urgency of the symptoms and signs presented by the patient. These responses will guide the NCM-Patient-PCP interaction. 'Red flag' answers require immediate contact to the PCP to discuss and undertake further steps.

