## **Digital structured blood glucose testing**

Additionally, digital structured blood sugar testing (using Roche Diagnostics' Accu Chek® Smart Pix Device and ACCU-Chek® 360°) is applied after T1 for symptom monitoring in 3-monthly interval (in total 3 times) (Figure 1). The NCM collects the individual blood sugar profiles, transfers them into the ICW Care Manager and reports the profiles to the PCP in charge of respective patients. The blood sugar profiles serve as basis for the telephone coaching.

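### Secondary outcome 4 (hypoglycemia): the T1–T2 at-risk set is chosen after randomization, and non-severe events are likely to be recorded more often in the intervention arm

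*Protocol*

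**What the plan says.** Chapter 2, Secondary outcomes, item 4 sets the endpoint as "The cumulative incidence of physician-reported (severe) symptomatic hypoglycemia at T1/T2 among those patients at risk of this event during the respective observation period". The item then defines its terms. The term used for a non-severe event "refers to hypoglycemia with blood glucose < 60 mg/dl"; those counted as severe are the ones "which necessitated external support". A patient counts as at risk "for the subsequent time period if they receive oral anti-diabetic medication and/or insulin therapy at To or T1". The same section says that events reach the trial database through a chart review by the practice. Chapter 10 schedules that review at T0, T1 and T2 and states no difference by arm.

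Section 3.1 fixes the timing: the baseline assessment "will be conducted prior to allocation of patients, and after allocation at 9 months" and again at 18 months. Chapter 4 states that neither patients nor practice teams can be blinded.

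Chapter 8 describes contacts that only the intervention arm (PTC) receives. On the telephone calls by the net-case manager (NCM) it says: "Monitoring items contain new diagnoses, dyspnea, incidence/frequency/severity of hypoglycemia, blood pressure, weight". Urgent (red-flag) answers must be passed to the practice at once. After T1 the NCM also collects three structured glucose profiles and "reports the profiles to the PCP in charge of respective patients". The control arm (TAU) has usual care, including disease-management visits up to every three months.

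Section 11.2 assigns this endpoint a two-level logistic model with a two-sided test at 0.05.

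**The concern.** There are two separate problems.

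**Denominator.** Medication at T1 is measured after nine months of an intervention that may change it. If patients start or stop medication at different rates in the two arms, the T1–T2 at-risk sets differ in composition for reasons other than chance. The comparison then loses the protection of randomization.

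**Detection.** A non-severe event counts only if a glucose value was taken and the physician knows of it. PTC has extra routes by which an event can become known to the practice. The same true event may therefore be recorded more often in PTC. Self-monitoring of glucose is also one of the behaviors the intervention aims to increase, so PTC patients may produce more qualifying values even before T1.

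Secondary objective 5 is this comparison. Section 3.2 also names possible effects on severe hypoglycemia as a main reason for adding glucose self-monitoring in patients not on insulin, and that element falls in T1–T2, where both problems are present. Unequal recording could make the intervention look harmful or hide a benefit.

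**Working it through.** **1. Which interval does the denominator problem touch?** The rule applies status at one visit to the period that follows.
- T0–T1 uses T0 medication, collected before allocation. It is a baseline variable, so there is no selection after randomization.
- T1–T2 uses T1 medication, collected nine months after baseline. This set is selected after randomization, as is any figure to T2 that relies on it.

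**2. How large could the denominator effect be?** The Protocol gives no incidence and no rate of medication change, so every input here is an assumption: 85% treated at T0 with risk 15% in T1–T2, and no true effect.
- Starters (share s, risk 5%): risk = (0.85 × 0.15 + s × 0.05) / (0.85 + s). With s = 10% in PTC: 0.1325 / 0.95 = 0.1395. With s = 2% in TAU: 0.1285 / 0.87 = 0.1477. Risk ratio 0.94.
- Stoppers (share s, risk 30%): risk = (0.85 × 0.15 − s × 0.30) / (0.85 − s). With s = 10% in PTC: 0.0975 / 0.75 = 0.130. With s = 0 in TAU: 0.150. Risk ratio 0.87.
- With the arms exchanged, the ratios become 0.1477 / 0.1395 = 1.06 and 0.150 / 0.130 = 1.15. The direction is therefore open.

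**3. How many extra contacts are there?** Calls every two weeks for 6 months give about 12, and monthly calls for the remaining 12 months give 12, which matches the stated total of 24. By T1 (month 9) the count is about 12 + 3 = 15. Structured glucose profiles begin only after T1.

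**4. How large could the detection effect be?** Observed risk = true risk × probability that an event is captured. Odds ratio = [p₁/(1 − p₁)] / [p₀/(1 − p₀)], with p₁ for PTC and p₀ for TAU. Capture rates are assumptions. True risk is 10% in both arms:

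| Capture PTC / TAU | Observed risk PTC / TAU | Observed OR |
|---|---|---|
| 90% / 80% | 9% / 8% | 1.14 |
| 60% / 40% | 6% / 4% | 1.53 |
| 80% / 50% | 8% / 5% | 1.65 |
| 90% / 50% | 9% / 5% | 1.88 |

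For example, 90/80: (0.09/0.91) / (0.08/0.92) = 0.0989 / 0.0870 = 1.14. The true risk matters little: at 5% and 20% the 90/80 case gives 1.13 and 1.15, and the 90/50 case gives 1.84 and 1.98.

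**5. What would that do to the test?** The Protocol has no sample-size figure for this endpoint. As an illustration I take 253 per arm, the evaluable number in Section 11.4, and a two-sided two-proportion z-test with no true effect and 10% true risk. The chance of a significant result is 5% with equal capture, 7% at 90/80, 25% at 90/60 and 42% at 90/50. The at-risk sets hold only treated patients and so are smaller, and the planned model differs, so these are indications only. In the other direction, a true risk ratio of 0.67 with 90/60 capture would appear as 0.67 × 0.90/0.60 = 1.01.

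**The case against.** The strongest reply has four parts.

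- **TAU is not unobserved.** Both arms have practice assessments with chart review and history taking at T0, T1 and T2 (Section 3.3.1), and all patients are in the diabetes disease-management program (Section 5.2). This stands: what TAU lacks is the NCM route, not every route.
- **The path into the chart is inferred.** The Protocol does not say which hypoglycemia answers are red flags, or that call findings are entered in the chart. The three profiles cover three days each, 9 of roughly 270 days after T1. The endpoint is labelled symptomatic, so an incidental low reading does not clearly count. This also stands, and it is why no single size can be given.
- **The endpoint is secondary.** Section 11.2 treats only the primary analysis as confirmatory and promises caution elsewhere, and Section 3.2 calls the glucose-monitoring question descriptive. This limits the consequence. But the stated caution concerns the number of tests, and it does not remove a systematic difference in recording.
- **T0 status changes the target population.** It keeps patients who stop medication and leaves out those who start. That is true, and it is a reason to keep the T1-based set as a sensitivity analysis.

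A reader might infer that post-randomization medication status undermines the whole endpoint. The text does not support that: the T0–T1 set uses status recorded before allocation. A reader might also infer that a detection bias of a known, large size is established. The documents contain no capture rates, and a mild difference gives an odds ratio close to 1.

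**Conclusion.** Both problems are real within limits.

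- **Denominator:** the T1–T2 comparison, as defined, is not between randomized groups. Direction and size are unknown; the assumed cases above give risk ratios of 0.87 to 1.15. The T0–T1 comparison is not affected.
- **Detection:** non-severe events are likely to be recorded more often in PTC in both intervals, through calls and home visits before T1 and also through glucose profiles after it. The size cannot be computed from the Protocol. With no true effect and 10% true risk, the observed odds ratio runs from about 1.1 (90% versus 80% capture) to about 1.9 (90% versus 50%). Severe events depend less on glucose testing and are less exposed, though the calls also ask about severity.

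The consequence is confined to the reading of secondary objective 5; the primary conclusion is untouched. Section 11 leaves detail to a statistical analysis plan that was not at hand, but the event and at-risk definitions are fixed in the Protocol itself, so the change should be made before the comparison is analyzed.

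**What to change.** 1. Define at-risk status by T0 medication for both intervals. Keep the T1-based set for T1–T2 as a sensitivity analysis.
2. Make severe events (external support needed) the main between-arm comparison, and note that the calls also ask about severity.
3. Report non-severe events descriptively by arm, and state the difference in detection as a limitation.
4. Optionally, have the T1 and T2 physician forms record how each event became known, and exclude events known only through the NCM or the study glucose profiles. Do this as a sensitivity analysis only: usual care might have found some of these events later, so excluding them from the main comparison could undercount PTC and reverse the bias.

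Items 1 to 3 need only wording. Item 4 needs one form field; the forms are listed in Chapter 18 but their content is not shown, so it may already be there. The price is fewer events in the main comparison, and patients who start medication between T0 and T1 are left out of the main T1–T2 set.

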### 3. Methods

#### 3.1 General Aspects

The study is designed as a prospective, multicenter, two-armed, open-label, individual-level randomized controlled superiority trial (RCT). Since the main elements of the intervention are delivered by an NCM (for details see Chapter 8: Intervention/Study Implementation), it is feasible to have both intervention and control group based in each study center (i.e. in each PCP).

Eligible participants will be randomly selected from the overall patient population of 30 study centers (PCPs) and asked for their consent to take part in the study. Participating patients will be reported pseudonymized to the study central office (Dept. for General Practice and Health Services Research, AMV) and centrally randomized on an individual level by a clinical monitor, who acts as sole randomization authority. This person - not involved in care of the trial patients or analysis of data - will be responsible for allocation to control (treatment as usual, TAU) vs. intervention group (pathway to change, PTC) according to a pre-defined randomization schedule (for details see Chapter 7: Randomization). As illustrated in Figure 1, the intervention is additional to usual care. Blinding of either patients or practice teams is not possible due to the character of the intervention. The baseline (To) assessment of primary and secondary outcomes will be conducted prior to allocation of patients, and after allocation at 9 months (primary endpoint: T1), and 18 months (follow-up: T2) (Figure 1).

Both intervention and control group receive usual care. Usual care consists of diabetes care in the scope of the DMP Diabetes. Care for high-prevalence chronic comorbidities such as chronic obstructive lung disease (COLD), heart failure (HF) and coronary heart disease (CHD) are also organized in the scope of DMPs on a voluntary basis in the statutory health insurance system (16). Care for other diseases (chronic or acute) is managed by PCP physicians individually based on personal experience, guidelines and/or patients' preferences.

Patients allocated to the PTC-group will be subject to the 18-month care management intervention as add-on to usual care. This complex care management intervention consists of three main elements (Figure 1):

- (i) assessments by a net-case manager (NCM) including home visits,
- (ii) regular telephone-monitoring contacts and
- (iii) digital structured blood glucose monitoring (introduced after T1).

Within the first week after entry to the study, the NCM visits patients in the PTC group at home to conduct a standardized assessment of medical and non-medical problems (see Appendix: Studienhilfsmittel Formular „Erstkontakt Assessment“). The results of the assessment are reported to the physician in charge of caring for the patient via a designated dialogue assistant (DA) based at each PCP. DAs are HCAs tasked to facilitate communication between NCMs, PCPs and patients in both study arms.

In the second week, the patient visits his/her primary care physician in order to agree upon goals related to the identified problems. The goals will be documented and serve as the basis for the telephone-monitoring. A total of 24 telephone-monitoring sessions will occur according to the schedule presented in Figure 1 (every two weeks for a period of 6 months, once a month throughout the rest of the intervention period for patients in the PCT-group). The objective of the telephone-monitoring is to detect acute clinical needs and to provide support related to self-care goals and health care related issues. Follow-up home visits (FUPHV) will occur 6 months (FUPHV-1) and 12 months (FUPHV-2) after entry to the study for patients in the PTC-group (see Appendix: Studienhilfsmittel Formular „Folgekontakt Assessment“). Additionally, after 11 months, digital structured blood sugar testing is used for symptom-monitoring in a 3-months-interval (3 in total). The blood sugar profiles serve as the basis for the coaching of patients by the NCMs in the scope of the telephone-monitoring. NCMs support patients in the PTC-group to locate and access additional services within the health system or the broader community according to patients' individual preferences and needs.

A preceding, unpublished scoping review (29) conducted by the investigators identified relevant determinants of diabetes self-care to be considered as potential confounders in the context of this RCT. These include general demographical aspects (sex, age, marital status/domestic partnerships), the individual social status (education, income, occupation), cultural factors potentially related to the migration status, type of comorbidity (e.g. discordant ones such as depression (11, 30) and/or arthrosis), type of diabetes therapy (insulin vs. oral medication), perceived quality of health care, alcohol abuse and emotional distress. The potential confounders will be captured at To-T2 as PROs. We further account for the type of medical therapy (insulin vs. oral medication/no medication) during the randomization process through stratified randomization (see Chapter 7: Randomization). For a full list of instruments and variables used in this study see Table 1 and Table 2.

Study findings will be reported according to the CONSORT 2010 checklist with extensions for PROs in RCTs (31).

